## 2.0 Study Hypothesis and Objectives

---

### 2.1 Hypothesis

The introduction of a men's malignancy survivorship programme into routine follow up care will be feasible and will result in improved symptom management and quality of life in patients with advanced genitourinary cancers.

Should this intervention prove feasible, we plan to use the data generated from this feasibility study as the basis for a Quality Improvement (QI) initiative for our patients in the future, by offering this programme to all of our patients as a standard component of clinical care.

### 2.2. Primary Objective:

- To demonstrate the feasibility of introducing a men's cancer survivorship programme into routine follow up care in patients with advanced genitourinary malignancies.

### 2.3. Secondary Objectives:

- To evaluate the impact of the survivorship programme on quality of life.
- To evaluate the impact of the survivorship programme on cancer related fatigue.
- To evaluate the impact of the physiotherapist and dietetic intervention on body weight, lean body mass, fat mass, muscle strength and nutritional risk over the study period.
- To evaluate the impact of a dietetic intervention by assessing changes in dietary intake and diet quality over the study period.
- To evaluate the impact of the survivorship programme on self-care agency and its relationship to quality of life and symptoms experienced.
- To assess the resource utilisation of signposted services and economic impact of a men's cancer survivorship programme.
- To explore and assess the satisfaction of patient and Health Care Professionals with the programme and to determine their perceptions of the systems usability.
- Explore participants' experiences of the intervention focusing on feasibility:
  - the perceived effectiveness of intervention components
  - acceptability of study and intervention procedures
  - the relations between implementation, mechanisms, and context
  - the barriers and facilitators to support effective implementation of future interventional programmes such as this one.

### 3.0 Study Plan & Endpoints

#### 3.1 Design:

Embedded Mixed-Method Process Evaluation.

This realist process evaluation using a mixed methods design (informed by the Medical Research Council) seeks to address the context of the pilot study, mechanisms of actions, and factors that influence the outcomes of the study i.e. “what works, for whom, under what circumstances” [5,6]. The information gleaned will explain how the intervention worked and how these effects might be replicated in a Quality Improvement (QI) initiative for our patients in the future, by offering this intervention to all of our patients as a standard component of clinical care.

The process evaluation will use the LOGIC model to systematically and visually present, map and share our understanding of the relationships among the resources used to underpin the intervention, the activities planned (intervention inputs, processes, actions) and outputs, outcomes, and impact [5].

Figure 1: Flowchart for LIAM Mc Trial

[figure not shown]

#### 3.2 Anticipated Study timeline:

The study will commence with a scoping review of the published literature to identify clear knowledge gaps and gain an understanding of supportive care interventions previously tested and effectiveness trials/interventions to support men with urological cancer. By conducting a scoping review, the research team will be able to identify the nature of a broad field of evidence in this area to inform the study. This will inform the Initial Phase involving 6 men with advanced prostate cancers. The number of participants is due to Covid-19 health precautions, the availability of the necessary exercise and measurement equipment, and with a view to promoting personalized care plans and to ensure both safety and the best programme possible for these men.

## The LIAM Mc Trial

This initial phase, 12-week programme of the first 6 men will be completed and analysed, including follow up and analysis, prior to commencement of the Expansion Phase from Q3 of year 1 onwards, see 3.2.1, Gantt Chart.

In the Expansion Phase, and for the remainder of the study period, parallel sampling groups will be used (i.e. after completion of the 6 participant Initial Phase). A new group of 6 participants will commence the programme every 6 weeks, in order to facilitate workload and resource management, see Figure 2. This will mean two groups are at two different timepoints in the programme at any given date. In total, 12 groups of 6 men are planned, including the initial phase group, with a total anticipated accrual of 72 participants over the two-year study period.

Data collection will occur at three designated timepoints; Baseline/Screening, and End of Treatment visit (after completing the intervention) and at 6 months post intervention. Completion of a process evaluation as part of the feasibility testing and secondary outcome measurement will also occur after all participants have completed the 12-week intervention programme.

**Subject recruitment:** June 2023-June 2025.

**Subject follow up period:** September M 2023-l December 2025 (12-18 months recruitment until 72 patients recruited + 6 months follow up for last patient enrolled)

Final data analysis: February 2026-

### 3.2.1 Overlapping Cohorts in the Expansion Phase

[figure not shown]

### 3.3 Primary Study Endpoint:

The primary endpoint of this study is to determine the feasibility and acceptability of introducing a men's cancer survivorship programme into routine follow up care in patients with advanced genitourinary malignancies.

The programme acceptability will be measured with each participant at programme completion and at the 6-month post intervention timepoint. PPI feedback at quarterly engagement meetings will also contribute to understanding the level of acceptability of and support for the study. To determine feasibility of such a multi-disciplinary project, success is multifactorial, and this will be reviewed by the Steering Committee throughout the project and during the scheduled PPI engagement meetings to inform subsequent phases. Qualitative interviews where participant

feedback is provided and the final analysis by the steering and research groups in conjunction with key stakeholders will all contribute to the final determination of the feasibility of the programme. This will help explore what elements of the intervention worked, what elements did not work, and what elements require improvement. A purposefully designed brief feasibility questionnaire will be used in line with previously developed questionnaires by our team [7]. This will be created as part of the scoping review.

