##### Survey Questions

The survey will include open-ended questions asking if the participant had any comments about their experience of participating in the intervention/study; elements of the intervention that worked/didn't work and changes they would like to make.

Other process evaluation data will be collected during the study e.g. timing and difficulties experienced with program components, frequency of adverse events (if any), implementation problems. Implementation problems identified during the study will be catalogued as they arise including the mechanisms by which issues are addressed.

Participants will be asked to complete a brief feasibility questionnaire adapted from Zellinger et al (2015) and based on the work of [name] and [name] (both co-applicants) [7], to assess the applicability, acceptability, practicality and relevance of the intervention. The survey will include Likert scale items relating to satisfaction with intervention components.

Qualitative semi structured individual and focus group interviews involving intervention participants and HCPs working within the broader interdisciplinary team will be conducted. The research team including the interventionalists, PPI representatives and key stakeholders (e.g. NCCP representative [name]) will be asked to partake in individual interviews to glean the perspectives of those delivering the intervention and the wider context into which the intervention is delivered.

A semi-structured interview guide will guide an open, in-depth interview with participants about their experience of the trial/intervention, how participants made sense of the intervention, the acceptability of the interventions, their engagement in the processes of the interventions, and the barriers and facilitators encountered.

In addition the interviewer will explore the mechanisms through which the intervention brings about changes which is crucial to understanding both how the effects of the specific intervention occurred and how these effects might be replicated by similar interventions in the future (MRC, 2015).

Context includes anything peripheral to the intervention that may influence its implementation, reach, or its effects. Thus, understanding the context is critical to understanding the potential impact of context on the implementation of the intervention.

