#### **4.4.7 Withdrawal/Discontinuation of Subjects**

All patients who initiate the study will be included in the overall analysis. All reasons for discontinuation of participation in the trial will be documented clearly in the trial record.

The reasons for discontinuation may include:

- a) At subject's own request.

Note: The reason for discontinuation from the study must be documented.

- b) Death.
- c) Intercurrent illness or condition that would, in the judgment of the principal investigator, affect assessment of clinical status to a significant degree.
- d) Evidence of disease recurrence during study.
- e) Study is terminated for any reason.
- f) Subject withdraws consent for follow-up.

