## The LIAM Mc Trial

|                                                                               |   |   |   |   |   |   |   |   |   |   |   |   |   |   |   |
|-------------------------------------------------------------------------------|---|---|---|---|---|---|---|---|---|---|---|---|---|---|---|
| Signposting to Other Services                                     | X | X | X | X | X | X | X | X | X | X | X | X | X | X | X |
| Social Work Education                                             |   |   |   | X |   |   |   |   |   |   |   |   |   |   |   |
| Nutritional Assessment/Education                                  |   |   | x |   | X |   | x |   | X |   | X |   |   |   |   |
| Occupational Therapy/physiotherapy                                |   |   |   |   |   | X |   |   |   |   |   |   |   |   |   |
| Nurse led education                                               |   |   |   |   |   |   |   | X |   |   |   |   |   |   |   |
| Pastoral care (spirituality & emotional reasoning)                            |   |   |   |   |   |   |   |   |   | X |   |   |   |   |   |
| Usability, Feasibility & Satisfaction Feedback questionnaires    |   |   |   |   |   |   |   |   |   |   |   |   |   | X |   |
| PPI workshop invitation and Invitation to Qualitative Interview  |   |   |   |   |   |   |   |   |   |   |   |   |   | X |   |
| Qualitative Interview (not all participants)                                  |   |   |   |   |   |   |   |   |   |   |   |   |   | X | X |

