Feasibility outcomes will be similarly described. These include the number of enrolled patients who complete the baseline and follow-up assessments, and the number of patients who partake in all planned activities versus less than all; the number of patients that require medical review and the timeframe to Medical review; changes in muscle strength and mass from baseline to end of programme assessments; changes in dietetic assessments from baseline to end of programme assessments; changes in QOL outcome measures from baseline to end of programme assessments; the number of patients enrolled in the programme; extra Health Care Professional time required and resources required for the intervention; and reasons for not completing the programme will be collected through Drop Out Forms and with qualitative discussions with HCP involved in the programme.

Missing data will be evaluated, and based on what we observe, dealt with in whatever manner we find appropriate based on current best practices. All analyses will be conducted using the R Project for Statistical Computing and the RStudio IDE. All trial reporting will be done following CONSORT and the CONSORT addendum for pilot/feasibility trials [22].

All analyses will be conducted and/or supervised by the HRB CRF-C Principal Statistician ([name]), under their established quality systems and SOPs, and in accordance with *ICH E9 Statistical Principles for Clinical Trials* and *ICH E6 Good Clinical Practices*.

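### Acceptability is to be measured with each participant at programme completion and at 6 months, but the Schedule places its questionnaire at End of Treatment only, with no timepoint for men who leave early.

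*Protocol*

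**What the plan says.** Protocol section 3.3 opens: "The primary endpoint of this study is to determine the feasibility and acceptability of introducing a men's cancer survivorship programme". On timing it says: "The programme acceptability will be measured with each participant at programme completion and at the 6-month post intervention timepoint". The same section adds feedback from patient-involvement meetings, qualitative interviews and a brief feasibility questionnaire. Section 4.4.4 (Survey Questions) says that this questionnaire is meant "to assess the applicability, acceptability, practicality and relevance of the intervention".

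In the Schedule of Activities (section 5.0) the matching row is "Usability, Feasibility & Satisfaction Feedback questionnaires". It has one mark, at EoT. The row "Qualitative Interview (not all participants") is marked at EoT and at 6 months. The notes to the Schedule place EoT assessments in the last programme week or up to two weeks after completion.

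For men who leave, section 6.2 says that "reasons for not completing the programme will be collected through Drop Out Forms", together with discussions with staff. Section 4.4.7 says: "All patients who initiate the study will be included in the overall analysis". It then lists possible reasons for discontinuing, among them intercurrent illness, "Evidence of disease recurrence during study" and, as a separate item, withdrawal of consent for follow-up.

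**The concern.** Sites work from the Schedule. If they follow it, the structured acceptability rating is taken once, and the 6-month measurement promised in section 3.3 is not made for each participant. This is a matter of data collection, so no later analysis can recover it.

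The single timepoint is also one that a man reaches only by staying to the end. Leaving early may itself be related to acceptability, since men who find the programme too demanding are plausible leavers. A rating taken only at EoT would then describe completers. Section 2.1 intends to use the results as the basis for offering the programme to all patients as standard care, so it matters which men the ratings describe.

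**Working it through.** **1. Endpoint text against Schedule.** The Schedule has 15 timepoint columns: screening, weeks 1 to 12, EoT and 6-month follow-up.

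| Source | Completion / EoT | 6 months | Who |
|---|---|---|---|
| Section 3.3, acceptability | yes | yes | each participant |
| Section 5.0, questionnaire row | marked | empty | men who reach EoT |
| Section 5.0, interview row | marked | marked | a subset |

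The empty cell does not look like a text-extraction gap, because the interview row in the same part of the table carries both marks.

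**2. Can other text supply the 6-month value?** Sections 4.4 and 4.4.5 mention questionnaires or surveys at 6 months without naming them. The questionnaires that the Schedule marks there are the EORTC QLQ-C30, the ASAS-R, the EORTC fatigue score and the food frequency questionnaire. None of these measures acceptability of the programme. The interview guide does cover acceptability (section 4.4.4), but interviews are optional (section 4.4.4.3) and limited to about twenty patients (section 4.4.8):

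- share of all planned men: 20 / 72 = 27.8%
- share of the 60 men the sample size is built on: 20 / 60 = 33.3%

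These are ceilings, because the same interviews may take place at EoT or at 6 months.

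**3. The plan's own numbers.** Section 6.1 sets 60 men so that a process failure occurring 5% of the time is detected with 95% confidence. The formula gives n = ln(1 − 0.95) / ln(1 − 0.05) = 58.4, rounded up to 59. With 60 men the probability of seeing at least one such failure is 1 − 0.95^60 = 0.954. The figure of 60 is therefore reproduced to within one man. The allowance for attrition is 72 − 60 = 12 men, and 12 / 72 = 16.7%.

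**4. How much could missing ratings matter?** The protocol gives no expected acceptability proportion, so 90% and 80% are assumptions. Suppose that 60 men give a rating and 12 do not. The lower bound counts all 12 as finding the programme unacceptable, and the upper bound counts all 12 as finding it acceptable.

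| Assumed among 60 respondents | Lower bound, all 72 | Upper bound, all 72 |
|---|---|---|
| 90% (54 men) | 54 / 72 = 75.0% | (54 + 12) / 72 = 91.7% |
| 80% (48 men) | 48 / 72 = 66.7% | (48 + 12) / 72 = 83.3% |

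In either case the range is 12 / 72 = 16.7 percentage points wide. It shows how uncertain the figure would be; it does not estimate a bias.

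**The case against.** The strongest reply is that acceptability does not rest on one questionnaire. Section 3.3 also draws on interviews and patient-involvement meetings, and interviews covering acceptability are marked at 6 months. This is correct, so it would be wrong to infer that nothing about acceptability is collected at 6 months. But an optional interview with up to twenty men is not a measurement with each participant.

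A reader might also infer that men who drop out are never asked. The documents contradict this. Drop Out Forms record their reasons, and section 4.4.8 invites all patients to give feedback once their involvement ends, with no restriction to completers. What is missing is a scheduled structured rating.

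A third tempting reading is that the primary endpoint as a whole is biased. That is not shown. Section 6.2 counts completion of assessments, participation in all or fewer activities, and reasons for not completing among the feasibility outcomes, so a man who leaves does enter the feasibility assessment. The selection concerns the questionnaire ratings.

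Nor does section 4.4.7 say that assessment stops when a man discontinues because of illness or recurrence. It lists withdrawal of consent for follow-up separately, and section 4.4.7.1 speaks of withdrawing from the intervention, so continued follow-up is not ruled out. The section is unclear on this and no more than that.

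Finally, acceptability has no stated weight. The synopsis and section 2.2 name feasibility only, and section 3.4 lists this questionnaire under a secondary endpoint. The 12 men are an allowance and not a forecast, and section 4.4.7.1 permits some early leavers to be replaced. These points limit the size of the concern but leave the mismatch between sections 3.3 and 5.0 in place.

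**Conclusion.** The point holds in a limited form. Section 3.3 requires acceptability from each participant at two times, while the Schedule provides a structured measure at one. At 6 months the only scheduled item that addresses acceptability reaches at most 28% of the planned men. The questionnaire also has no scheduled timepoint for men who leave before EoT, so its ratings will probably over-represent completers. That direction is a judgement and cannot be proved from the documents.

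Under the assumptions of 60 respondents, 12 men without a rating, and 90% acceptability among respondents, the figure for all 72 lies between 75% and 92%; at 80% it lies between 67% and 83%. The mismatch itself depends on none of these assumptions.

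**What to change.** - **Reconcile sections 3.3 and 5.0.** The better option is to mark this questionnaire in the 6-month column and collect it with the questionnaires already due then. The alternative is to remove the 6-month timepoint from section 3.3, which restores consistency but gives up the later measurement.
- **Men who stop early.** Send the same short questionnaire with the Drop Out Form.
- **Section 4.4.7.** Add a sentence that stopping the programme does not by itself end the EoT and 6-month questionnaires unless consent for follow-up is withdrawn.
- **Reporting.** Give acceptability with the number of respondents out of all enrolled men.

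The cost is one Schedule cell, one sentence and a short form that can go by post, by email or with the existing 6-month call. The burden on men who have stopped is slight. Some will decline, so the gap will narrow but not close.

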### 3.4 Secondary Study Endpoints:

1. Impact of the survivorship programme on quality of life.
  - EORTC QLQ C30 will be administered at baseline and at the end of the 12-week programme.
  - Quality-adjusted life-year (QALY) (EQ-5D-5L)
  - ASAS-R assessment
  - Additional Assessments as identified by the scoping review will be included in the Expansion Phase.
2. Impact of the survivorship programme on cancer related fatigue.
  - Cancer related fatigue score(EORTC QLQ-FA12).
3. Impact of the programme physiotherapy and dietetic interventions:
  - Maintenance of weight (weight measurement); changes in body composition (lean body mass and fat mass as measured by Bioelectrical Impedance Analysis [BIA]); muscle strength and mass (8 repetition maximum, thigh circumference); physical function and cardiovascular fitness (grip strength, 6 minute walk test [6MWT]).
  - An analysis of body composition analysis using US for muscle mass assessment compared to BIA in a subset of men participating in the study.
  - Changes in dietary intake and diet quality over the study period resulting from the dietetic intervention.
  - Dietary assessments will be conducted by a dietitian. This includes two 24 Hour Dietary Recalls and the WCRF food checklist at baseline and the programme endpoint (12 weeks) and a Food Frequency Questionnaire at baseline and 6 month follow up.
4. Self-care agency and its relationship to quality of life and symptoms experienced.
  - Instruments to measure self-care agency include the ASAS-R
  - Additional Assessments as identified by the scoping review will be included in the Expansion Phase.
5. The resource utilisation of signposted services among participants in the 12-week intervention programme.
  - Quality-adjusted life-year (QALY) (EQ-5D-5L)
  - Resource utilisation (number of signposted resources used). (See section 4.4.4)
6. Satisfaction of participants and Health Care Professionals with the programme and their perceptions of the systems usability.

## The LIAM Mc Trial

- Usability, Satisfaction and Feasibility Questionnaire
- Participants, health care professionals and the broader team involved in the development and implementation of the programme will be invited to provide feedback after the completion of their involvement in the study through qualitative interviews.

## 4.0 Methods

This multi-disciplinary programme will span the hospital system, University and community services. Patients will be recruited predominantly via the Medical Oncology outpatient clinics, see Figure 1, Flowchart. The Patient Information Leaflet (PIL) will be provided to the interested party and upon enrolment the participant will provide Informed Consent.

### 4.1 Inclusion Criteria:

1. Men aged  $\geq 18$  years of age at the time of study enrolment.
2. Willing to participate in a 12-week intervention programme and follow up procedures as outlined in the Schedule of Activities section.
3. ECOG performance status 0-2.
4. Recovery to CTCAE Grade  $\leq 2$  adverse events from all prior therapies, or adequately recovered adverse events whereby, whereby the PI feels they will not impact the participants ability to complete the 12-week intervention.
5. Disease-specific inclusion criteria:

